## Abstract

**Background:**

Prolonged disorders of consciousness (PDOC) may occur after severe brain injury. Two diagnostic entities are distinguished within PDOC: unresponsive wakefulness syndrome (UWS, previously known as vegetative state) and minimally conscious state (MCS). Patients with PDOC may benefit from early intensive neurorehabilitation (EIN). In the Netherlands, the EIN programme is provided by one designated expert rehabilitation centre and forms the starting point of a dedicated chain of specialised rehabilitation and care for this group. This study project, called DOCTOR: Disorders of Consciousness; Treatment and Outcomes Registry, sets up a registry and systematically investigates multiple short- and long-term outcomes of patients with PDOC who receive EIN.

**Methods:**

Single-centre prospective cohort study with a 2-year follow-up period. Patients with PDOC due to acute brain injury who receive EIN, aged 16 years and older are included. Measurements will take place at start EIN, in week 5, 10, and at discharge from the EIN programme (duration = max 14 weeks) and at week 28, 40, 52, and 104 after admission to the EIN programme, following patients through the health-care chain. Outcome measures are the changes over time in level of consciousness, using the Coma Recovery Scale-Revised; the frequency and type of medical complications; the mortality rate; level of disability, including the level of motor, cognitive, behavioural and emotional functioning; participation; and quality of life. Secondary outcomes include self-efficacy of caregivers, caregivers’ strain and cost-effectiveness of the programme.

**Discussion:**

The DOCTOR study will provide insight in the recovery patterns and predictors of recovery for multiple outcomes in PDOC patients after following EIN. The results of the study will enable us to benchmark and improve EIN and the organisation of the health-care chain, both for patients with PDOC and for their families.

**Trial registration:**

Netherlands Trial Register, NL 8138. Retrospectively registered 6 November 2019.

## Background

Prolonged disorders of consciousness (PDOC) (> 4 weeks) due to acquired brain injury (ABI) although uncommon [1, 2] have a major impact on patients and their families [3]. Two diagnostic entities are distinguished within PDOC: the unresponsive wakefulness syndrome (UWS, previously known as vegetative state) and the minimally conscious state (MCS) [4, 5]. In UWS, persons display spontaneous eye opening and sleep/wake cycles, but observable signs of purposeful behaviour (e.g. language comprehension, behavioural response to stimuli) are absent [6]. Patients in MCS demonstrate minimal but definitive behavioural evidence of awareness. Conscious behaviour in MCS is often subtle and inconsistent, and must be systematically differentiated from reflexive or random behaviour [6]. Based on the complexity of behaviour, a differentiation is made between MCS-minus (MCS-) and MCS-plus (MCS+) [7, 8]. MCS+ is distinguished from MCS- by the evidence of language processing [7]. PDOC can arise from various aetiologies, but the most common causes in adults are traumatic brain injury, intracerebral and subarachnoid haemorrhage and hypoxic-ischemic encephalopathy [4, 9, 10]. Hypoxic-ischemic encephalopathy is the most common cause in UWS patients (38–50%) [9, 11], while cerebral haemorrhage is most common in MCS [9]. Van Erp et al. reported a prevalence of 0.1 to 0.2 hospitalised and institutionalised UWS patients per 100,000 members of the general Dutch population [11] while worldwide prevalence varies from 0.2 up to 6.1 per 100,000 [1]. PDOC patients may benefit from subacute neurorehabilitation, such as early intensive neurorehabilitation (EIN). EIN focuses on (1) basic care and prevention of complications [12] (e.g. thrombo-embolic disease, contractures, skin breakdown, paroxysmal sympathetic hyperactivity), which cause a substantial raise in morbidity, discomfort and pain, and in healthcare costs [13]; (2) accurate assessment and treatment aimed to facilitate recovery of level of consciousness (LOC); (3) finally, providing comprehensive education and empowerment of families to foster families’ coping.

Research on recovery shows that 38 and 78% of patients with PDOC due to traumatic brain injury (TBI) regain (minimal) consciousness at respectively 3 and 12 months post injury [2]. In patients with non-traumatic brain injury (NTBI) only 17% regains consciousness at 8 months post injury [2]. Aidinoff et al. [14] demonstrated an improvement in survival and recovery of consciousness in UWS patients over the last two decades after EIN, and similar outcomes for both TBI and NTBI UWS. These outcomes suggest that improvements in acute medical care and EIN have contributed to advances in UWS care. Treatment started within 8 weeks after injury is associated with better outcomes in terms of LOC and functioning, gained in a faster pace than treatment started after 8 weeks [15–17]. In patients with PDOC of mixed aetiology with a mean time follow-up of 5 years, 40% of survivors reached functional independence, while 42% of patients able to respond to a self-report questionnaire, reported a poor quality of life [18]. The EIN programme in the Netherlands has been studied before; in patients aged < 25 years recovery of consciousness occurred in two-thirds at the end of the EIN programme [19] and two-thirds of the patients who were fully conscious at discharge were able to live independently after 10–12 years [20].

Prognostic factors associated with better recovery from PDOC are younger age at onset, traumatic aetiology, less severe comorbidities and less severe neurological impairment, i.e. higher level of consciousness at admission to EIN [2, 4, 15, 21–25]. However, most studies on recovery after PDOC suffer from methodological issues, such as a retrospective design [2] and variability in clinical decision making in acute care [2]. Further, research on outcomes after PDOC often fails to discriminate between diagnostic subtypes (UWS or MCS), aetiology and the time since injury [2]. Furthermore, data on quality of life, costs and cost-effectiveness of rehabilitation programmes, and caregiver burden are limited.

The **D**isorders **o**f **C**onsciousness **T**reatment and **O**utcomes **R**egistry (DOCTOR) is a prospective follow-up study on outcomes for all patients ≥16 years in UWS and MCS and their families who entered the EIN programme in one designated expert rehabilitation centre in the Netherlands. It is a 14-week subacute intensive neurorehabilitation programme for patients discharged from the intensive care unit or hospital ward, to improve (recovery of) consciousness, prevent complications and empower caregivers.

In DOCTOR outcomes of patients with PDOC are recorded systematically with a follow-up of 24 months after admission to EIN. Main outcome measures are (predictors) of recovery of LOC, mortality, incidence and type of complications, outcomes in terms of level of disability, including the level of motor, cognitive, behavioural and emotional functioning, pain, cognition, participation and quality of life. Further, caregiver burden and self-efficacy will be assessed as well as cost-effectiveness.

## Methods

### Study design and setting

The DOCTOR study is a nationwide single-centre prospective cohort study with 2 years follow-up. Measurements take place at start EIN, in week 5, 10, and at discharge of the EIN programme (duration = max 14 weeks) and at week 28, 40, 52, and 104 after admission to the EIN programme, following patients through the health-care chain. (Fig. 1).

**Fig. 1 Fig1:**
[figure not shown]
Study design

The EIN programme is standard care and is provided in a single specialised rehabilitation centre in the Netherlands. All hospitals in the Netherlands may refer patients who are eligible for EIN to this centre. Informed consent is obtained from the legal representative of each patient before the start of the study. Patients who show sufficient recovery of consciousness during the study trajectory will personally be asked consent for further participation in the study.

This study is not subject to the “Medical Research Involving Human Subjects Act”, determined by the Medical Ethics Committee of Erasmus MC, University Medical Centre Rotterdam (MEC-2019-0127).

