### Data collection

In 4 years we aim to include 72 patients. Structured data collection (Fig. 3) will take place at the start of the EIN programme at week 5, 10, and at EIN discharge (week 14). LOC assessment and registration of complications will be done weekly.

After discharge from EIN, follow-up measurements are planned at 28, 40, 52, and 104 weeks post-inclusion. These will take place at the patients’ actual health-care institution or residence.

All measurements conducted during the EIN programme are performed by trained members of the rehabilitation team. Follow-up measurements are performed by a trained research assistant.

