### Statistical analysis

Descriptive statistics will be used to present the outcomes of the study parameters and the socio-demographic data. Means and standard deviations will be calculated for variables on an interval scale and medians and interquartile ranges for ordinal variables. Proportions will be calculated for nominal variables.

Subgroup analyses will be performed for patients presenting in UWS versus MCS at baseline and for traumatic versus non-traumatic disorders of consciousness.

The proportions of patients transitioning from UWS to MCS and emergence from MCS to the conscious state will be calculated during and after EIN.

The course of recovery of consciousness (yes/no) over time will be analysed using Generalized Estimating Equations (GEE) analysis for logistic outcomes on an intention-to-treat basis. Assuming that data are missing at random, data imputation is unnecessary in GEE analysis; all observations are taken into account in contrast to complete case analyses. Recovery (yes/no) at each time point will be included as the dependent variable in the GEE model. Separate models will be generated for transitions from UWS to MCS and from MCS to the fully conscious state based on the CRS-R. Independent variables that will be added one by one to the models, include- measurement time (weeks), traumatic vs. non-traumatic aetiology, age at injury, and complications (yes/no or number). Significant predictors (*p* < 0.05) will be included in a multivariable model using a Bonferonni correction, dividing the significance level (alpha< 0.05) by the number of predictors included in the model.

Also using GEE analysis, the course of quality of life (EQ-5D-5L and Qolibri) and participation (CIQ) over time will be analysed using separate linear outcome models. The effects of time, cognitive (MoCa), behavioural (NPI), emotional (HADS), and motor status (FIM), and level of disability (DRS) and discomfort (NCS) on quality of life or participation during follow-up will be studied by adding these time-dependent variables (one by one) as independent variables to the models. Significant predictors (*p* < 0.05) will be added into a multivariable GEE-model to study the independence of these potential predictors on the outcomes using the Bonferroni correction.

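### Asking only recovered patients for a new consent makes exit depend on the outcome, and the planned unweighted GEE does not correct for it

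*Protocol article*

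**What the plan says.** Under Methods, Study design and setting, consent has two stages. First: "Informed consent is obtained from the legal representative of each patient before the start of the study". Then: "Patients who show sufficient recovery of consciousness during the study trajectory will personally be asked consent for further participation in the study". The level of recovery that counts as sufficient is not defined, and no second consent step is described for patients who do not reach it.

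The Statistical analysis section fixes the outcome: "Recovery (yes/no) at each time point will be included as the dependent variable in the GEE model". Two models are planned on the CRS-R, one for UWS to MCS and one for MCS to full consciousness. On missing data it sets GEE against an analysis restricted to complete cases: "Assuming that data are missing at random, data imputation is unnecessary in GEE analysis; all observations are taken into account in contrast to complete case". It also plans a simpler summary: "The proportions of patients transitioning from UWS to MCS and emergence from MCS to the conscious state will be calculated during and after EIN".

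The visits at risk are mainly the late ones. Data collection states: "After discharge from EIN, follow-up measurements are planned at 28, 40, 52, and 104 weeks post-inclusion".

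**The concern.** Asking patients who regain capacity for their own consent is proper and is not the issue. The issue is how that step combines with the stated analysis. The decision to stay is put again only to patients who have recovered. A refusal therefore takes a patient last known to be recovered out of later visits. It cannot take out a patient who never recovered.

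The protocol's stated safeguard does not cover this. Dropout that follows a recorded recovery is missing at random at best. Ordinary GEE is in general valid only when data are missing completely at random, or when missingness depends only on covariates in the model. Under the broader missing-at-random assumption that the article invokes, GEE needs weights or imputation, or else a likelihood model should replace it.

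At stake is the course of recovery to week 104, a main outcome. The model for MCS to full consciousness is the most exposed, because patients able to consent are most likely to be those who have emerged. Patients who passed from UWS through MCS to consciousness and then decline would also leave the first model. Later EQ-5D-5L, QOLIBRI, CIQ, MoCA and HADS data come largely from the same patients and could be lost selectively.

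**Working it through.** The article gives no refusal, dropout or death rate, so there is no planned figure to reproduce. The sample size is a recruitment target only: "In 4 years we aim to include 72 patients".

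**Formula.** Let p be the true proportion recovered at a visit, r the share of recovered patients who declined, and d the share of unrecovered patients lost, for example by death. Then

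observed proportion = p(1 − r) / [p(1 − r) + (1 − p)(1 − d)].

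The values of r and d are assumptions throughout.

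**Refusal alone (d = 0), 72 patients, 36 truly recovered (p = 50%, assumed).**

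- r = 10%: 32.4 / 68.4 = 47.4%
- r = 20%: 28.8 / 64.8 = 44.4%
- r = 30%: 25.2 / 61.2 = 41.2%

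The shifts are 2.6, 5.6 and 8.8 points. They do not depend on the total of 72.

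**Refusal alone, at recovery rates quoted in the Background.** These come from other cohorts and other definitions (some count minimal consciousness), so they serve only as a range for p.

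| True p | r = 10% | r = 20% | r = 30% |
|---|---|---|---|
| 17% (non-traumatic, 8 months) | 15.6% | 14.1% | 12.5% |
| 38% (traumatic, 3 months) | 35.6% | 32.9% | 30.0% |
| 66.7% (earlier EIN cohort) | 64.3% | 61.5% | 58.3% |
| 78% (traumatic, 12 months) | 76.1% | 73.9% | 71.3% |

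The third row rests on: "in patients aged < 25 years recovery of consciousness occurred in two-thirds at the end of the EIN programme".

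**Does GEE repair it?** A large-sample simulation followed the protocol's visit schedule. Recovery was monotone and reached two-thirds at week 104, and refusal occurred only after recovery had been recorded. Logistic GEE with visit as a category gave these week-104 estimates (true value 0.666):

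| Working correlation | r = 20% | r = 30% |
|---|---|---|
| Independence | 0.616 | 0.585 |
| Exchangeable | 0.646 | 0.630 |

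The bias is smaller under exchangeable correlation but does not vanish. The article does not fix the structure.

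**Adding loss of unrecovered patients.** In the formula the net bias is zero when r = d. With p = 50% and r = 20%:

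- d = 20%: 0.40 / (0.40 + 0.40) = 50.0%
- d = 40%: 0.40 / (0.40 + 0.30) = 57.1%

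In the simulation with r = 20%, the observed week-104 proportion was 0.670 at d = 20% and 0.728 at d = 40%, against 0.667 among all enrolled. The sign can reverse.

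**Using recovery already recorded.** Counting patients as ever recovered, with data before refusal kept, the simulation gave 0.67 at every r from 0 to 30%.

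**Weighting.** With p = 50%, r = 20% and no deaths, each recovered patient who remains gets weight 1/0.8 = 1.25. Then 28.8 × 1.25 = 36, and 36/72 = 50%.

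**Scale.** At n = 72 and p = 2/3, the 95% half-width is 1.96 × √(2/3 × 1/3 / 72) = 0.109, about 11 points.

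**The case against.** The strongest reply has four parts.

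- **Direction.** A reader might infer that late recovery will be underestimated because unrecovered patients all stay. The documents do not support that. No refusal rate is given, and the Mortality section expects deaths, including after non-treatment decisions and withdrawal of artificial nutrition and hydration. If those fall mainly on unrecovered patients, they remove negative records. This stands: the net direction is undetermined. It does not rescue the plan, since the two exits cancel only by coincidence and unweighted GEE corrects neither.
- **Trigger.** The threshold for re-consent is undefined and is not tied to either modelled transition. This stands, and is why the concern is placed mainly in the second model.
- **Recovery is usually recorded first.** Level of consciousness is assessed weekly during EIN and again at each follow-up visit. The planned transition proportions need not be biased if data before refusal are kept. This largely stands. The exception is a patient who recovers and declines between visits; the last two are 52 weeks apart.
- **Unshown documents.** Data retention and consent tiers may be set out in the full protocol or consent form, so their absence here is not a finding. Nor does the article say that decliners leave mortality follow-up. Both stand. The reasoning that missingness at random makes imputation unnecessary in GEE is different: the article states it itself.

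The shifts are also below the sampling half-width. That is true, but they are systematic.

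**Conclusion.** The concern holds in a conditional form. Re-consent triggered by recovery builds in an exit that depends on the outcome, and the stated analysis of per-visit recovery does not in general correct it. If 10 to 30% of recovered patients decline and nobody else is lost, a true 50% reads 2.6 to 8.8 points low in observed proportions. GEE with an exchangeable structure shows a smaller shift: 0.646 against 0.666 at week 104 with 20% refusal.

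Three stronger readings are not supported. Overall underestimation cannot be asserted, because deaths act in the opposite direction. A false decline is not shown: in the simulation the curve still rose at every refusal rate tried. Bias in all recovery analyses is not shown either, because the transition proportions can escape it.

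The result rests on assumed refusal and death rates and, in the simulation, on no relapse. The mechanism is clear; its size is not. It is worth correcting because the remedy is cheap, but it does not undermine the study.

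**What to change.** 1. **Consent.** At re-consent, offer a minimal tier beside full participation, limited to level of consciousness and vital status from routine records. State what counts as sufficient recovery.
2. **Analysis.** Keep data recorded before the patient's decision. Analyse recovery as time to, or cumulative incidence of, first recorded recovery with death as a competing event. Alternatively, keep the per-visit model but weight GEE by the inverse probability of remaining in the study, with a separate stated rule for deaths.
3. **Text and reporting.** Drop the statement that missingness at random makes imputation unnecessary in GEE. Report refusals by recovery status.
4. **Sensitivity analysis.** Vary the assumed status of decliners after exit, including relapse. In the 72-patient example with 20% refusal and no deaths, there are 7.2 decliners. If none relapse the estimate is 36/72 = 50%. If 10% relapse it is 35.28/72 = 49.0%. If all relapse it is 28.8/72 = 40%. Simply carrying recovered status forward is not enough, because it tests neither relapse nor death after exit.

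The cost is one extra option on the consent form, modest analysis work, and an assumption about status after exit that the sensitivity analysis tests.

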### In- and exclusion criteria

Patients with PDOC due to acute brain injury who are admitted to the EIN programme are possible candidates for this study. At admission to EIN, patients will be screened for eligibility for DOCTOR. Patients are included in DOCTOR if the in- and exclusion criteria are met (Table 1).

**Table 1 Tab1:** Inclusion and exclusion criteria

**Inclusion criteria**	
Age16 years or older	
PDOC (UWS or MCS) lasting > 4 weeks and < 6 months at admission to EIN	
First-time newly acquired non-progressive brain injury of any aetiology	
Weaned from ventilator	
Medically stable, as judged by the treating rehabilitation physician	
**Exclusion criteria**	
Coma	
Any pre-existent progressive or non-progressive brain injury	
Uncontrollable epilepsy	

### EIN programme

The EIN programme is a subacute medical rehabilitation programme of 14 weeks (or less when recovery of consciousness occurs earlier) and meets the guideline recommendations for patients with PDOC published by the American Academy of Neurology [26]. An interdisciplinary rehabilitation team of a rehabilitation physician, a physician assistant, a neuropsychologist, cognitive rehabilitation therapists, physiotherapists, occupational therapists, speech therapists, nursing staff, dietician, and social worker uses an integrated approach in a 24/7 setting [19] with a minimum duration of 120 min therapy per day in which daily routines are built in together with a structured scheme of therapy and rest. The program is focused on optimizing the metabolic state, nourishment, respiration and skin condition, as well as diminishing the risk of infections and quick removal of invasive devices, like a tracheostomy tube or a urinary catheter, and recovery of the normal circadian cycle. Pharmacological treatments and structured stimulation of all sensory modalities (vision, hearing, smell, taste, touch, posture and motion, pain and temperature) aim to generate maximal arousal. As soon as the patient shows any voluntary reactions, reflecting a change from UWS into MCS, the focus of treatment changes from stimulation to training of cognitive functions. Motor rehabilitation aimed at optimising postural and motor activity helps restore bodily integrity and reduces the risk of complications (e.g., infection, thrombo-embolic complications, skin breakdown). For patients who reach MCS, increased time is spent on training mobility and self-care. Coping and self-efficacy of caregivers are addressed with psychoeducation, counselling and hands-on training in handling the patient.

After EIN, patients are discharged to 1) a regular neurorehabilitation setting in case of full recovery of consciousness and the ability to participate in a rehabilitation programme as judged by the rehabilitation physician, 2) to skilled nursing facilities, 3) sheltered housing or 4) possibly home (Fig. 2). Some skilled nursing facilities offer a prolonged intensive neurorehabilitation programme (PIN) for further recovery of consciousness during a period of up to 24 months post-injury. EIN is part of an academic network of expertise (EENnaComa) in which various healthcare institutes specialised in post-acute and long-term care of PDOC patients and their families are united.

